# Stereotactic ablative radiotherapy for the comprehensive treatment of 4–10 oligometastatic tumors (SABR-COMET-10): study protocol for a randomized phase III trial

**DOI:** 10.1186/s12885-019-5977-6

**Published:** 2019-08-19

**Keywords:** Oligometastases, Stereotactic radiotherapy, Quality of life, Cancer, Survival

## Abstract

**Background:**

Stereotactic ablative radiotherapy (SABR) has emerged as a new treatment option for patients with oligometastatic disease. SABR delivers precise, high-dose, hypofractionated radiotherapy, and achieves excellent rates of local control for primary tumors or metastases. A recent randomized phase II trial evaluated SABR in a group of patients with a small burden of oligometastatic disease (mostly with 1–3 metastatic lesions), and found that SABR was associated with benefits in progression-free survival and overall survival. The goal of this phase III trial is to assess the impact of SABR in patients with 4–10 metastatic cancer lesions.

**Methods:**

One hundred and fifty-nine patients will be randomized in a 1:2 ratio between the control arm (consisting of standard of care palliative-intent treatments), and the SABR arm (consisting of standard of care treatment + SABR to all sites of known disease). Randomization will be stratified by two factors: histology (Group 1: prostate, breast, or renal; Group 2: all others), and type of pre-specified systemic therapy (Group 1: immunotherapy/targeted; Group 2: cytotoxic; Group 3: observation). SABR is to be completed within 2 weeks, allowing for rapid initiation of systemic therapy. Recommended SABR doses are 20 Gy in 1 fraction, 30 Gy in 3 fractions, or 35 Gy in 5 fractions, chosen to minimize risks of toxicity. The primary endpoint is overall survival, and secondary endpoints include progression-free survival, time to development of new metastatic lesions, quality of life, and toxicity. Translational endpoints include assessment of circulating tumor cells, cell-free DNA, and tumor tissue as prognostic and predictive markers, including assessment of immunological predictors of response and long-term survival.

**Discussion:**

This study will provide an assessment of the impact of SABR on clinical outcomes and quality of life, to determine if long-term survival can be achieved for selected patients with 4–10 oligometastatic lesions.

**Trial registration:**

Clinicaltrials.gov identifier: NCT03721341. Date of registration: October 26, 2018.

**Electronic supplementary material:**

The online version of this article (10.1186/s12885-019-5977-6) contains supplementary material, which is available to authorized users.

## Background

The *oligometastatic state* refers to a stage of disease where a cancer has spread beyond the site of the primary tumor, but is not yet widely metastatic [1]. In patients with a limited oligometastatic burden, emerging evidence suggests that treatment of all sites of disease with ablative therapies (such as surgery or stereotactic radiation) can improve patient outcomes, including overall- and progression-free survival.

Historically, evidence to support the oligometastatic state has consisted of single-arm, non-randomized studies without controls. One classic study reported on over 5000 patients with lung metastases from a variety of primary tumors. In patients who achieved a complete resection of their lung metastases, 5-year overall survival (OS) was 36%, better than might be expected for a cohort of patients with metastatic disease [2]. Similarly, after radiation, a recent pooled analysis of 361 patients with oligometastatic lesions treated with radiation demonstrated a 3-year OS of 56% [3].

It has been suggested the long-term survivals achieved in patients with oligometastases after ablative therapies is merely due to the selection of very fit patients with slow growing tumors, since randomized evidence to support the oligometastatic paradigm has been lacking [4, 5]. However, at least four recent randomized phase II trials now provide some supporting evidence of an oligometastatic state.

### Randomized evidence supporting the oligometastatic state

Two of these four randomized trials were done in the setting of oligometastatic non-small cell lung cancer (NSCLC). In both, patients presented with a primary lung tumor and a limited number of metastatic lesions (1–3 in one trial, 1–5 in the other), and after initial systemic therapy, patients were randomly assigned to standard palliative treatments vs. consolidative ablative treatments to all sites of disease. Both trials were stopped early due to evidence of efficacy, with the ablative treatments achieving a ~ 3-fold improvement in progression-free survival (PFS) [6, 7]. Based on these results, the phase III NRG LU-002 trial is assessing the impact of consolidative ablative therapies on OS.

A third trial, EORTC 40004, examined the impact of an ablative therapy (radiofrequency ablation [RFA]) in patients with colorectal cancer metastatic to the liver. In this trial, patients with a controlled primary tumor and fewer than 10 hepatic metastases not amenable to resection, and with no extra-hepatic disease, were randomized to systemic therapy +/− RFA to all sites of disease [8]. When initially reported [9], the trial showed no difference in OS between arms, but with long-term follow-up (median 9.7 years), a significant difference in OS emerged, with an 8-year OS of 36% in the RFA arm and only 9% in the systemic therapy arm [8].

The fourth trial, Stereotactic Ablative Radiotherapy for the Comprehensive Treatment of Oligometastatic Disease (SABR-COMET) enrolled 99 patients who had controlled primary solid tumors and up to 5 metastatic lesions [10–12]. Patients were randomized in a 1:2 ratio between standard of care (SOC) palliative treatments (Arm 1) vs. SOC + SABR to all sites of disease (Arm 2). The primary endpoint was OS, and the trial employed a randomized phase II screening design, with an alpha of 0.20, in order to provide an initial comparison between arms. More than 90% of patients enrolled had 1–3 metastases. OS was 28 months in Arm 1 and 41 months in Arm 2 (*p* = 0.09), meeting the primary endpoint of the trial. PFS was doubled: 6 months in Arm 1 and 12 months in Arm 2 (*p* = 0.001). SABR was generally well tolerated, with a 29% rate of grade 2 or higher toxicity, although the rate of treatment-related grade 5 toxicity was 4.5%.

Despite this new evidence, many uncertainties remain regarding the oligometastatic state.

### Defining the oligometastatic state

A major unanswered clinical question is the precise definition of the oligometastatic state, namely, how many metastatic lesions are amenable to ablative therapies that may benefit the patient.

Many studies have defined ‘oligometastatic’ as 1–3, or 1–5, metastatic lesions, although some have used broader definitions, including the EORTC 40004 trial described above that allowed up to 9. For example, one single-arm phase II trial in patients with NSCLC enrolled 24 patients with up to 6 active sites of extracranial disease, and treated patients with SABR to all active sites along with erlotinib. The treatment was well-tolerated, with only two grade 3 toxicities. Median OS was 20.4 months, and median PFS was 14.7 months. A second study included NSCLC patients with up to 8 lesions, as long as all could be treated within established dose constraints [13].

In the setting of brain metastases, recent non-randomized evidence suggests that patients may benefit from stereotactic radiotherapy to 4–10 metastatic lesions. The prospective JLGK0901 trial treated 1194 patients who had 1–10 metastatic lesions, with a total cumulative volume of ≤15 mL, and treated all with stereotactic radiosurgery. The study used a non-inferiority design with a primary endpoint was OS, comparing patients with 5–10 lesions vs. those with 2–4. Median OS in both groups was 10.8 months, meeting the primary endpoint of non-inferiority (*p* < 0.0001). Treatment was well-tolerated, with only 9% of patients in either group experiencing adverse events of any grade. A separate retrospective study examined stereotactic radiation in patients with more than 10 brain metastases (where 64% had received prior brain radiotherapy), and concluded that it could be delivered safely, with no episodes of symptomatic necrosis and a 13% rate of radiographic necrosis [14].

The toxicity of SABR may not depend on the overall number of lesions, but moreso the doses delivered to organs at risk. For serial organs, such as the spinal cord, bronchi, and great vessels, reduction of the maximum dose of radiation is expected to reduce the risk of toxicity. For parallel organs, such as the lung, liver and renal cortex, the risk of toxicity may be mitigated by ensuring that a critical volume of the organ is spared from substantial doses of radiation [15]. The typical critical volume to be spared is about 1/3 of the volume of the organ. Therefore, this trial will employ dose constraints for serial structures that ensure minimization of high-dose volumes, constraints for parallel structures that ensure critical volume sparing, and constraints for dose spillage, to ensure that all SABR plans are highly conformal.

The application of ablative therapies for patients with 4–10 metastatic deposits appears promising, based on the encouraging results from randomized trials mostly enrolling patients with 1–3 lesions and the single-arm studies evaluating ablative therapies patients with a larger burden of disease. However, it is likely that as the number of metastases increases, the risk of further distant failure (i.e. development of additional metastases after SABR) will increase, and the risk of toxicity from SABR will likely increase. As a result, the use of SABR in such patients might be best in a scenario where the doses of SABR are lowered to reduce the risk of toxicity, pre-planning of SABR is required before enrollment, and SABR is given immediately prior to systemic therapy that will help to address the risk of occult micrometastases.

In summary, it is unclear if all patients with > 3 oligometastatic lesions benefit from SABR, in terms of improved OS, PFS, or quality of life. The purpose of this randomized trial is to assess the impact of SABR on outcomes in patients with 4–10 oligometastatic lesions.

## Methods/design

The objective of this trial is to assess the impact of SABR, compared to standard of care treatment, on overall survival, oncologic outcomes, and quality of life in patients with a controlled primary tumor and 4–10 metastatic lesions.

### Primary endpoint

Overall Survival
◦ Defined as time from randomization to death from any cause

### Secondary endpoints

Progression-free survival
◦ Defined as time from randomization to disease progression at any site or deathTime to development of new metastatic lesionsQuality of life
◦ Assessed with the Functional Assessment of Cancer Therapy: General (FACT-G) and the EuroQol - 5 Dimension - 5 Level (EQ-5D-5L)Toxicity
◦ Assessed by the National Cancer Institute Common Toxicity Criteria (NCI-CTC) version 4 for each organ treated (e.g. liver, lung, bone)

### Translational endpoints

Assessment of circulating tumor cells, cell-free DNA, and tumor DNA as prognostic and predictive markers of survival, and for early detection of progressionAssessment of immunological predictors of response and long-term survival

## Study design

This study is a phase III multicentre randomized trial. Participating centres will be tertiary, academic hospitals or radiotherapy treatment centres in Canada, the United Kingdom, the Netherlands, and Australia (updated country list available on ClinialTrials.gov entry NCT03721341). Patients will be randomized with parallel assignment in a 1:2 ratio between current standard of care treatment (Arm 1) vs. standard of care treatment + SABR (Arm 2) to sites of known disease (Fig. 1).

**Fig. 1 Fig1:**
[figure not shown]
Study Schema

Patients will be stratified by two of the strongest prognostic factors, based on a large multi-institutional analysis [3]: histology (Group 1: prostate, breast, or renal; Group 2: all others), and type of pre-specified systemic therapy (Group 1: immunotherapy/targeted; Group 2: cytotoxic; Group 3: observation).

## Inclusion criteria

Age 18 or olderWilling to provide informed consentKarnofsky performance status > 60Life expectancy > 6 monthsHistologically confirmed malignancy with metastatic disease detected on imaging. Biopsy of metastasis is preferred, but not required.Controlled primary tumor
◦ Defined as at least 3 months since original tumor treated definitively, with no progression at primary siteTotal number of metastases 4–10All sites of disease can be safely treated based on a pre-plan

## Exclusion criteria

Serious medical comorbidities precluding radiotherapy. These include interstitial lung disease in patients requiring thoracic radiation, Crohn’s disease in patients where the gastrointestinal (GI) tract will receive radiotherapy, and connective tissue disorders such as lupus or scleroderma.For patients with liver metastases, moderate/severe liver dysfunction (Child Pugh B or C)Substantial overlap with a previously treated radiation volume. Prior radiotherapy in general is allowed, as long as the composite plan meets dose constraints herein. For patients treated with radiation previously, biological effective dose calculations should be used to equate previous doses to the tolerance doses listed below. All such cases must be discussed with one of the study PIs.Malignant pleural effusionInability to treat all sites of diseaseAny single metastasis > 5 cm in size.Any brain metastasis > 3 cm in size or a total volume of brain metastases greater than 30 cc.Metastasis in the brainstemClinical or radiologic evidence of spinal cord compressionDominant brain metastasis requiring surgical decompressionMetastatic disease that invades any of the following: GI tract (including esophagus, stomach, small or large bowel), mesenteric lymph nodes, or skinPregnant or lactating women

## Pre-treatment evaluation

### Investigations

History and Physical Examination
◦ Including prior cancer therapies and concomitant cancer-related medicationsRestaging within 12 weeks prior to randomization:
◦ Brain: CT or MRI for tumor sites with propensity for brain metastasis. All patients with brain metastases (at enrollment or previously treated) require an MRI.◦ Body: 18-FDG PET/CT imaging is recommended, except for tumors where FDG uptake is not expected (e.g. prostate, renal cell carcinoma). PSMA-PET or choline-PET is recommended for prostate cancer. In situations where a PET scan is unavailable, or for tumors that do not take up radiotracer, CT neck/chest/abdomen/pelvis with bone scan required◦ Spine: MRI required for patients with vertebral or paraspinal metastases. The MRI needs to image the area being treated and one vertebrae above and below as a minimum, but does not need to be a whole spine MRI unless clinically indicated.Liver function tests (AST, ALT, GGT, alkaline phosphatase), albumin, bilirubin, and INR for patients with liver metastasesPregnancy test for women of child-bearing age

### Defining the number of metastases

#### Counting Metastases

Patients are eligible if there are 4–10 metastatic lesions present. Each discrete lesion is counted separately. For patients with lymph node metastases, each node is counted as one site of metastasis. All known metastatic lesions must be targetable on planning CT. For patients where the lesion is only detectable on MRI, fusion of the MRI with the planning CT is required. There is no limit to the number of metastases in each individual organ, as long as dose constraints can be met in the pre-plan. For parallel organs such as the liver and lung, patients with several lesions may not meet the pre-plan criteria and therefore will not be randomized.

#### Previously treated metastases

Patients with prior metastases that have been treated with ablative therapies (e.g. SABR, surgery, radiofrequency ablation) are eligible, as long as those metastases are controlled on imaging. In that case, the previously treated lesions are counted toward the total of 10 (e.g. a patient with 3 previous brain metastases treated is allowed to have up to 7 other metastases for enrollment).

If a patient has received systemic therapy and the number of metastases has been reduced, they are eligible for enrollment as long as the total number of metastases prior to systemic therapy was 10 or fewer.

#### Small or indeterminate lesions

When patients have small indeterminate nodules (e.g. a 3 mm lung nodule) it can be difficult to determine whether these are benign or whether they represent metastasis. Any such indeterminate lesion is automatically considered to be a metastasis *unless there are > 2 months of documented stability.* The presence or absence of such indeterminate lesions will be noted on the study enrollment form.

If a lesion is too small to treat due to targeting issues (e.g. a 3 mm lung lesion not likely to be visible on cone beam CT [CBCT]), the following approach is to be taken: if randomized to Arm 1, no intervention is needed, since such a lesion would not require palliative radiation. If randomized to Arm 2, the lesion is followed, and upon progression to a size that is treatable, it should be treated with SABR. This would not be counted as progression.

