### Assessment of efficacy

Overall Survival
◦ Defined as time from randomization to death from any causeProgression-free survival
◦ Defined as time from randomization to disease progression at any site or death.◦ Progression is defined as per the Response Evaluation Criteria in Solid Tumors (RECIST) 1.1 guidelines (http://recist.eortc.org/recist-1-1-2/). It can be difficult to distinguish recurrence from fibrosis/pseudoprogression after stereotactic radiation in some locations, such as the lung or brain. In such cases, if the RECIST 1.1 criteria for progression are met, the situation should be counted as progression unless there is imaging follow-up with stability of the imaging findings for at least 6 months.◦ As per RECIST 1.1, when findings of progression are equivocal (e.g. small new lesions of uncertain etiology), the patient should still be followed. If progression is confirmed at the next assessment, the date of progression assigned is the earlier date when progression was first suspected.Time to development of new metastatic lesions
◦ Defined as the time from randomization to the development of new lesions that were not detectable at the time of randomization. In a situation where indeterminate lesions were present at randomization, progression at one of those lesions does not count as a new metastatic lesion.◦ As noted above, as per RECIST 1.1, when findings of new metastases are equivocal (e.g. small new lesions of uncertain etiology), the patient should still be followed. If progression is confirmed at the next assessment, the date of progression assigned is the earlier date when progression was first suspected.Quality of life
◦ Assessed with the Functional Assessment of Cancer Therapy: General (FACT-G) and the EQ-5D-5 LToxicity
◦ Assessed by the National Cancer Institute Common Toxicity Criteria (NCI-CTC) version 4 for each organ treated (e.g. liver, lung, bone)]

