### Interim analysis

The DSMC will conduct one interim analysis once the 75th patient is accrued and followed for 6 months. For this interim analysis, the DSMC will be blinded to the identity of each treatment arm, but median OS data will be presented for each arm. The DSMC will recommend stopping the trial if there is an OS difference that is statistically significant with a threshold of *p* < 0.001 using the stratified log-rank test.

It is deemed worthwhile to stop for futility if both the OS and PFS analyses are likely to be negative. Therefore, at this interim analysis, if the hazard ratios for OS and PFS in Arm 2 vs Arm 1 are BOTH > 1.0 (i.e. a higher hazard rate for OS in the experimental arm, and a higher hazard rate for PFS in the experimental arm) using univariable Cox regression, then the trial will be stopped for futility.

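### Growth of a lesion too small to target is exempt from progression in the SABR arm only, so the PFS event definition differs by arm, with a bias towards SABR that is probably small to modest

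*Protocol article*

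**What the plan says.** Under Small or indeterminate lesions (within Pre-treatment evaluation), the protocol first says of small nodules without documented stability: "Any such indeterminate lesion is automatically considered to be a metastasis". It then deals, arm by arm, with a lesion too small to target.

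- Arm 1: "if randomized to Arm 1, no intervention is needed, since such a lesion would not require palliative radiation". Nothing is said about whether later growth counts as progression.
- Arm 2: the lesion is followed and, once it has grown to a treatable size, "it should be treated with SABR. This would not be counted as progression".

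PFS is defined once for both arms under Assessment of efficacy: "Defined as time from randomization to disease progression at any site or death". The criterion follows: "Progression is defined as per the Response Evaluation Criteria in Solid Tumors (RECIST) 1.1 guidelines". No exemption for these lesions appears there. That section does have a rule on indeterminate lesions that applies to both arms, but it belongs to a different endpoint, time to new metastatic lesions.

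PFS is a secondary endpoint compared by stratified log-rank test (Analysis plan). It is also one of two inputs to the futility rule (Interim analysis), which stops the trial if both hazard ratios exceed 1.0, that is, "a higher hazard rate for OS in the experimental arm, and a higher hazard rate for PFS in the experimental arm".

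**The concern.** A between-arm comparison of time to event needs one definition of the event. Here a lesion left untreated at baseline in both arms can grow by the same amount and produce a PFS event in Arm 1 but none in Arm 2. The exemption can only remove events from Arm 2, so any distortion favours SABR.

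Two results depend on it. The PFS comparison could show a slight advantage for SABR where none exists. At the interim analysis, a PFS hazard ratio above 1.0 becomes somewhat less likely, so the PFS condition for stopping is met less often.

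**Working it through.** **Reading the text.** The exempting sentence directly follows the Arm 2 instruction. It refers to growth followed by SABR, a sequence that this subsection sets out for Arm 2 only. The PFS definition is common to both arms and adds no exemption. Followed literally, growth of such a lesion that meets RECIST 1.1 is an event in Arm 1 and is exempt in Arm 2.

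**The plan's own figure.** The protocol gives no PFS assumption or PFS event count, so there is no PFS figure to reproduce. The trial is sized on OS: medians of 10 and 17 months, 1:2 allocation, 122 events. Taking the 0.05 alpha as two-sided, power is Φ(√(122 × 2/9) × ln(17/10) − 1.96) = Φ(5.207 × 0.5306 − 1.96) = Φ(0.803) = 0.789, in line with the stated 80%. That sizing does not depend on the present point. The same formula is used below.

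**Illustrative size.** All inputs here are assumptions:

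- no true PFS effect, and constant hazards;
- hazard h = ln 2 / median for all other PFS events, with a median of 6 months (the control-arm PFS quoted for the earlier SABR-COMET trial) or 4 months (patients here have more lesions);
- a share q of patients with one such lesion, and a growth hazard g of 0.03 to 0.116 per month that is independent of other progression;
- all such growth counted in Arm 1 and none in Arm 2;
- hazard ratio taken as the ratio of events per person-month over 24 months.

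Per patient in Arm 1:

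- events = (1−q)(1−e^(−24h)) + q(1−e^(−24(h+g)))
- person-months = (1−q)(1−e^(−24h))/h + q(1−e^(−24(h+g)))/(h+g)

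The Arm 2 rate is h, so the apparent hazard ratio is h divided by the Arm 1 rate.

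Example with median 6, q = 10%, g = 0.116: h = 0.1155 and h+g = 0.2315. Events = 0.9 × 0.9375 + 0.1 × 0.9961 = 0.9434. Person-months = 0.84375/0.1155 + 0.09961/0.2315 = 7.734. The Arm 1 rate is 0.9434/7.734 = 0.1220, and the hazard ratio is 0.1155/0.1220 = 0.95.

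| Median PFS | q | g = 0.03 | g = 0.06 | g = 0.116 |
|---|---|---|---|---|
| 6 months | 5% | 0.99 | 0.98 | 0.97 |
| 6 months | 10% | 0.98 | 0.96 | 0.95 |
| 4 months | 5% | 0.99 | 0.99 | 0.98 |
| 4 months | 10% | 0.99 | 0.97 | 0.96 |

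**Effect on the PFS test.** The chance of a significant result favouring SABR when there is no effect is Φ(√(D × 2/9) × |ln HR| − 1.96), nominally 0.025. With an assumed D = 122 PFS events it is 0.028 at a hazard ratio of 0.99 and 0.045 at 0.95.

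**Effect on the futility rule.** The chance that the estimated PFS hazard ratio exceeds 1.0 is Φ(√(D × 2/9) × ln HR), which is 0.50 with no effect and no asymmetry. With an assumed 45 or 60 interim PFS events it is 0.49 (both counts) at 0.99, and 0.44 or 0.43 at 0.95. Stopping also requires the OS hazard ratio to exceed 1.0.

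**The case against.** The exempting sentence can be read differently. It may mean only that deferred SABR to a known baseline lesion completes the allocated strategy and is not salvage. Arm 1 has no such deferred treatment, so it would need no matching sentence, and the PFS definition itself is neutral between arms. That reading is possible, but the text speaks of what counts as progression, and assessors will apply what is written. If both arms were meant, one sentence makes it so.

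The objections on size are stronger, and they stand:

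- The affected group is narrowed elsewhere. The inclusion criteria require that all sites can be treated safely on a pre-plan, inability to treat all sites is an exclusion, and Counting Metastases requires known lesions to be targetable on the planning CT. The subsection still provides for lesions that are not, so the group is not empty, but nothing supports a share of 20 or 30%.
- Not all growth of a few-millimetre lesion would meet RECIST 1.1, and equivocal findings must be followed first.
- Such lesions may grow alongside the patient's other disease, so some of these patients would have a PFS event anyway.
- The top growth hazard, 0.116 per month, equals the whole assumed hazard from other causes at a 6-month median (ln 2/6 = 0.1155), which is high for one nodule.

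A reader might infer a serious distortion of PFS. With a 6-month median, the same calculation gives hazard ratios from 0.94 down to 0.84 if 30% of patients had such a lesion. The protocol gives no basis for that share. A reader might also infer that the primary result or the futility rule is compromised. OS does not use progression at all, and the asymmetry can change a futility decision only when the OS hazard ratio is already above 1.0, where it makes continuing more likely.

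**Conclusion.** The point holds as a defect in a stated endpoint rule: as written, PFS events are counted differently by arm, and the bias has one direction. The direction follows from the text; the size does not. Under the assumptions shown (no true effect, median PFS of 4 to 6 months, 5 to 10% of patients affected, growth hazard 0.03 to 0.116 per month) the apparent PFS hazard ratio is about 0.99 to 0.95. Because all growth is counted and treated as independent of other progression, these figures lean high for a given share and growth hazard. The bias is probably small to modest. OS and the sample size are unaffected. This should be fixed, because the repair is cheap and a futility decision cannot be corrected afterwards, but it does not threaten the trial's primary conclusion.

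**What to change.** Under Assessment of efficacy, state one PFS rule for lesions recorded before randomization as too small to target, and cross-reference it from Small or indeterminate lesions. Either choice removes the asymmetry:

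- count growth that meets RECIST 1.1 as progression in both arms, which keeps the general PFS definition intact; or
- exempt it in both arms, which keeps the stated Arm 2 rule and resembles the existing handling of indeterminate lesions for new metastases.

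Report the opposite rule as a sensitivity analysis, and apply the chosen rule to the interim PFS hazard ratio as well. It should be settled before the interim look.

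The enrollment form now records only the presence or absence of indeterminate lesions. It should also identify which lesions are too small to target, before randomization and for both arms.

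The cost is a sentence in the endpoint definition, a cross-reference and a small addition to the form. The PFS comparison may look slightly less favourable to SABR. Sample size and visits do not change, and neither does how the lesion is treated in either arm.
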